### Acupuncture interventions

2.9

After enrollment, patients in the VA and SA groups will receive an immediate acupuncture treatment for cowhage-induced pruritus during fNIRS scanning, followed by a long-term treatment of 12 sessions over 4 weeks (three sessions per week). Acupuncture points (Kim et al., 2010) in this trial include the bilateral: *Quchi* (LI11), *Hegu* (LI4), *Xuehai* (SP10), *Sanyinjiao* (SP6), *Zusanli* (ST36), and *Shenshu* (BL23).

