#### Inclusion criteria

2.4.2

Patients who match all the following items will be included:1) Meet the diagnostic criteria for UP and lasts for 6 weeks or longer, and 2) moderate to severe itch of UP (average weekly score of 24-h Worst Itch Numeric Rating Scale (24 h WI-NRS) in the past week≥ 4 points), and 3) aged 18 to 65 years with right-handed, and 4) have been regularly undergoing hemodialysis for more than 3 months, and 5) within the first 3 months before enrollment, at least one single chamber urea clearance rate (spKt/V) of ≥ 1.2 and urea decline rate (URR) of ≥ 65%, and 6) not combined with serious mental illness or cognitive impairment, and 7) not combined with neurological diseases such as cerebral hemorrhage and cerebral infarction, and 8) without alcohol or drug addiction, 9) medications for UP, such as antihistamines, gabapentin, topical emollients, and other antipruritic agents, need to maintain a stable dosage for at least 1 month before enrollment, and any newly increased antipruritic drugs are forbidden during the trial, and 10) not participating in other clinical trials currently, and 11) sign informed consent before conducting the trial.

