#### Exclusion criteria

2.4.3

Patients will be excluded if they:1) have other skin diseases that can cause itching, such as psoriasis, atopic dermatitis, urticaria, contact dermatitis, etc., and 2) suffer from any severe chronic liver disease, or any one of alanine aminotransferase, aspartate aminotransferase, glutamyltransferase, or total bilirubin exceeding twice the upper limit of normal values, and 3) with malignant tumors or other serious illnesses that require hospitalization, and 4) with severe mental illness or cognitive impairment (such as dementia), and 5) only experience itching during hemodialysis, and 6) have undergone physical therapy such as acupuncture or moxibustion within 1 month to address itching symptoms, and 7) present with coagulation dysfunction or local skin infection and ulceration, and 8) pregnant or lactating women.

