### Cowhage test for inducing pruritus

2.8

The primary neuronal transmission pathway of UP is mediated by non-histamine pathways. Hence, the cowhage test could induce acute pruritus in UP patients (Papoiu et al., 2014). According to previous studies (Zuo et al., 2023), about 20 cowhage spicules will be applied using a gloved finger to a 2 cm diameter area located about 5 cm below the elbow of the patient’s non-fistula forearm. The spicules will then be gently rubbed on the skin in a circular motion for 30 s. The itch-inducing procedure will take approximately one minute. Pruritus intensity will be assessed every minute for 5 min using a 0–10 visual analogue scale (VAS). After the test, spicules will be completely removed using adhesive tape.

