#### Instant acupuncture treatment

2.9.1

The instant acupuncture will be performed at acupoints using disposable sterile filiform needles (0.25 × 40 mm, Huatuo Medical Instrument Co., Ltd., China). In the VA group, the acupuncturist will remove the rubber ring from the patient’s skin at the base of the Park Sham Placebo Acquire Device (PSD) and attach the plastic sleeve to the acupoint surface. The needles will then be retained in the acupoints for 5 min during fNIRS scanning. In the SA group, patients will receive acupuncture using the PSD with blunt needles. Once the needle touches the skin, it will retract into the plastic sleeve of the PSD. No additional acupuncture manipulations will be performed, and the needle will remain on the skin for 5 min during fNIRS scanning.

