##### VA group

2.9.2.1

The PSD will also be used during long-term acupuncture treatment. After skin disinfection using alcohol, needles will be inserted to a depth of 20-30 mm. The acupuncturist will then twist the needle (90°-180°) and perform lift-thrust manipulations with an amplitude of 3-5 mm at a frequency of 1–1.5 Hz to induce needle sensations (soreness, numbness, distention, and heaviness). Each 30 min session includes 10–15 s of needle manipulation every 10 min to sustain the needle sensation.

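### LI11 and LI4 are fixed on both arms of hemodialysis patients with no exception for the access arm, an avoidable needling exposure of unknown risk

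*Protocol article*

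**What the plan says.** - **Population.** Section 2.4.2 requires that patients "have been regularly undergoing hemodialysis for more than 3 months".
- **Points and sessions.** Section 2.9 states that the points "in this trial include the bilateral: *Quchi* (LI11), *Hegu* (LI4"), together with SP10, SP6, ST36 and BL23. VA and SA patients have one instant session during the first fNIRS scan, "followed by a long-term treatment of 12 sessions over 4 weeks (three sessions per week").
- **VA technique, long-term sessions.** Under Section 2.9.2.1, "needles will be inserted to a depth of 20-30 mm". The acupuncturist also twists the needle and is to "perform lift-thrust manipulations with an amplitude of 3-5 mm at a frequency of" 1–1.5 Hz.
- **VA technique, instant session.** Section 2.9.1 says: "The needles will then be retained in the acupoints for 5 min during fNIRS scanning". No depth is given.
- **SA technique.** Section 2.9.2.2 uses the same points with blunt needles that do not puncture the skin.
- **Cowhage test.** Section 2.8 applies the spicules to an area "located about 5 cm below the elbow of the patient’s non-fistula forearm". It gives no reason for the choice of side.
- **Safeguards.** Section 2.4.3 excludes patients who "present with coagulation dysfunction or local skin infection and ulceration". Section 2.13 provides a safety assessment after every session. Neither mentions a fistula, a graft or an access arm.

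**The concern.** Section 2.8 presupposes that patients may have a fistula in one forearm, and it spares that forearm for a test on the skin surface. The next section then directs needles to both arms of every VA patient. The milder procedure is restricted by side and the penetrating one is not.

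What is at stake is patient safety. Section 2.13 itself names hematoma, bleeding and infection as events to watch for after acupuncture, and nothing in the plan limits where on the arms they could occur. The existing safeguards screen out some patients beforehand and detect events afterwards, but they do not keep needles off the access limb.

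There is also a secondary point, which is inference rather than a defect in the text. The acupuncturist is unblinded (Section 2.7). Without a written rule, an acupuncturist might spare the access arm case by case, perhaps more often with penetrating than with blunt needles. Those departures from Section 2.9 would not be recorded as such.

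**Working it through.** The plan gives no exposure figure, so there is none to reproduce. The count below uses its own inputs.

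**Inputs**
- Section 2.9: 6 points, all bilateral, of which LI11 and LI4 lie on the arm; 12 long-term sessions and 1 instant session.
- Section 2.5: 32 patients enrolled per group, 27 required before the 15% dropout allowance.
- Not given: f, the share of VA patients with an arm fistula.

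**Per VA patient with an arm fistula, as printed**
- Placements per session: 6 × 2 = 12.
- Sessions: 12 + 1 = 13.
- All placements: 12 × 13 = 156.
- Access arm: LI11 and LI4 on one side = 2 per session. Long-term 2 × 12 = 24; instant 2 × 1 = 2; total 26.
- Share: 26 / 156 = 16.7%.

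**The same patient with access-side LI11 and LI4 omitted**
- Placements per session: 12 − 2 = 10; over 13 sessions, 10 × 13 = 130.
- Access arm: 0.

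| | As printed | With the exception |
|---|---|---|
| Points per session | 12 | 10 |
| Arm points per session | 4 of 12 (33.3%) | 2 of 10 (20.0%) |
| Access-arm placements, 13 sessions | 26 | 0 |
| Instant session: needles on the cowhage limb | 2 | 2 |
| Instant session: needles on the opposite arm | 2 | 0 |

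**Whole VA group**
- Access-arm placements: 26 × 32 × f = 832f.
- f = 0 gives 0; f = 0.5 gives 416; f = 1 gives 832.
- The 832 assumes that all 32 patients attend all 13 sessions. Counting only 27 patients, the number before the dropout allowance, gives 26 × 27 × f = 702f.

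Only VA patients are punctured. In SA the sham device rests on the same arm sites without penetration, and the waiting-list (WT) group receives no acupuncture during the trial.

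**The case against.** The strongest reply is that this is a journal article. A one-sentence point list is a default set, and rules on which limb to avoid or what to do when a point cannot be used commonly sit in the full protocol or operating procedures, which are not shown. That possibility cannot be excluded. However, the article does not leave the side open: it fixes both sides. If an unseen rule exists, the published description of the intervention is inaccurate and the same sentence corrects it. If none exists, the exposure is real.

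Second, Sections 2.8 and 2.9 do not contradict each other, since both can be followed as written. The cowhage site may have been taken over from the earlier studies that Section 2.8 cites, or chosen for measurement reasons, and it spares a forearm rather than a whole arm. This stands. A safety motive is an inference, and extending the restriction to every point on the limb, LI4 included, is part of the assumption. What Section 2.8 does establish is that arm fistulas are foreseen in this population.

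Third, the documents contain no evidence that needling LI11 or LI4 endangers an access. The counts measure placements, and their range includes zero. This also stands and limits how strongly the point can be put. The exclusions, the checks after each session and the ethics approval (Section 2.2) bear on severity, but none of them removes the exposure.

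Fourth, the change alters the stimulus behind the mechanistic outcomes and reduces the number of points in an unknown share of patients. The pilot effect in Section 2.5 comes with no description of its points, so the effect of a 10-point regimen is unknown. This is a genuine cost.

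**Conclusion.** The concern holds as an avoidable safety exposure of unknown risk and should be fixed. Section 2.9, followed literally, places 26 needles in the access arm of each VA patient with an arm fistula, 24 of them at 20–30 mm with manipulation. An access-side exception brings this to 0.

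The conclusion rests on one assumption from outside the documents, that penetrating needles in an access arm are better avoided. It applies only to patients with an arm access, whose number the documents do not give. Neither harm nor bias is demonstrated. Confidence is medium, because the size of the risk is unknown and an operating rule may exist unseen.

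**What to change.** Add to Section 2.9:

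> In patients with a vascular access in an arm, neither needles nor the sham device will be applied to the access arm; LI11 and LI4 will be used on the non-access arm only. This applies identically to VA and SA, in the instant session and in all 12 long-term sessions.

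Add two CRF fields, the access side and the points delivered at each session, and use the recorded side in a sensitivity analysis of the fNIRS outcomes.

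**Cost.** One amendment sentence, two fields and one additional analysis. The sample-size calculation in Section 2.5 and the primary clinical model in Section 2.14.1 need no change.

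**Downside.**
- Affected patients receive 10 points instead of 12.
- Their arm stimulation becomes one-sided and falls on the cowhage limb, with the side varying by patient. This changes the input to the primary somatosensory cortex (S1), which Section 2.11 records on both sides. The needle count on the cowhage limb stays at 2; what is lost is the 2 on the opposite arm.
- Because the rule is the same in VA and SA, it does not bias that comparison. Contrasts with WT would describe a 10-point treatment with one-sided arm needling in these patients.

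Omitting LI11 and LI4 on both arms would keep the stimulation symmetric but leave only 12 − 4 = 8 points, so it is not proposed.

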#### Instant acupuncture treatment

2.9.1

The instant acupuncture will be performed at acupoints using disposable sterile filiform needles (0.25 × 40 mm, Huatuo Medical Instrument Co., Ltd., China). In the VA group, the acupuncturist will remove the rubber ring from the patient’s skin at the base of the Park Sham Placebo Acquire Device (PSD) and attach the plastic sleeve to the acupoint surface. The needles will then be retained in the acupoints for 5 min during fNIRS scanning. In the SA group, patients will receive acupuncture using the PSD with blunt needles. Once the needle touches the skin, it will retract into the plastic sleeve of the PSD. No additional acupuncture manipulations will be performed, and the needle will remain on the skin for 5 min during fNIRS scanning.

#### Long-term acupuncture treatment

2.9.2

##### VA group

2.9.2.1

The PSD will also be used during long-term acupuncture treatment. After skin disinfection using alcohol, needles will be inserted to a depth of 20-30 mm. The acupuncturist will then twist the needle (90°-180°) and perform lift-thrust manipulations with an amplitude of 3-5 mm at a frequency of 1–1.5 Hz to induce needle sensations (soreness, numbness, distention, and heaviness). Each 30 min session includes 10–15 s of needle manipulation every 10 min to sustain the needle sensation.

##### SA group

2.9.2.2

Patients in this group will receive treatment at identical acupoints as the VA group. While these patients’ skin will not be actually punctured by using blunt needles with PSD. During 30 min treatment, any other acupuncture manipulation will not be performed.

##### WT group

2.9.2.3

Patients assigned to the WT group will not receive any acupuncture treatment at the cowhage test or during the 4-week trial. After completing the trial, they can voluntarily choose whether to accept 12 sessions of free acupuncture treatment provided by our research group. To alleviate the impact of attention/expectation effects from clinical contact, WT participants will receive weekly telephone symptom monitoring by a blinded researcher. Retention strategies for this group include flexible scheduling for the post-trial free acupuncture, regular follow-up telephone calls, and transportation reimbursement.

### Clinical assessments

2.10

#### Instant itch intensity induced by the cowhage test

2.10.1

Patients will use VAS to rate itch intensity induced by the cowhage test during the first fNIRS scanning, with an evaluation per minute. The VAS scale ranges from 0 ~ 10, and the end-points anchoring the VAS are: 0 = no itch sensation, and 10 = maximum unbearable itch. The peak VAS itch score recorded during the observation period will be extracted for statistical analysis.

#### Primary clinical outcome

2.10.2

The weekly mean 24 h-WI-NRS scores at baseline and during each week of the 4-week trial period will be evaluated as the primary clinical outcome (Fishbane et al., 2020a, 2020b). The 24 h-WI-NRS scale ranges from 0 (no itch sensation) to 10 (maximum unbearable itch) points.

#### Secondary clinical outcomes

2.10.3

##### 14-item uremic pruritus in dialysis patients scale

2.10.3.1

Patients will use the 14-Item Uremic Pruritus in Dialysis Patients Scale to evaluate the quality of life from a multi-dimensions such as symptoms of pruritus, social psychology, and sleep, comprehensively reflecting their quality of life (Nochaiwong et al., 2024). The scores ≤12 mean mild damage, scores 13 ~ 21 represents moderate damage, and scores ≥22 represent severe damage to the quality of life. The scores at week 4 and the baseline period will be used for statistical analysis.

##### Psychological condition

2.10.3.2

Since patients with UP are frequently accompanied by mental disorders (Faucon et al., 2025), the Patient Health Questionnaire-9 (PHQ-9) and Generalized Anxiety Disorder Scale-7 (GAD-7) will be used to evaluate their emotional state before and after this trial. PHQ-9 score ranges from 0 ~ 4, 5 ~ 9, 10 ~ 14, 15 ~ 19, and 20 ~ 27, corresponding to no, mild, moderate, moderately severe, and severe depression, respectively. GAD-7 score ranges from 0 ~ 4, 5 ~ 9, 10 ~ 14, and≥15, being classified as no, mild, moderate, and severe anxiety, respectively.

### Core neuroimaging indicator: fNIRS data acquisition

2.11

Based on the efficacy of acupuncture for UP, this study will further focus on its central mechanism. According to previous studies (Mochizuki and Kakigi, 2015; Sun, 2025), we hypothesize that acupuncture’s antipruritic effect of UP correlates with modulation of cortical regions involved in itch processing, particularly the prefrontal cortex (PFC) and primary somatosensory cortex (S1), which can be captured in real-time by portable fNIRS. Moreover, considering that the oxyhemoglobin (HbO) signal has a better signal-to-noise ratio and is more reliable and sensitive than the deoxyhemoglobin signal (Strangman et al., 2002; Dravida et al., 2018), this trial will use cortical HbO changes to characterize the functional activity of PFC and S1, two regions of interest (ROIs). Therefore, the HbO change of task-state scanning data during the first fNIRS scan will be the primary outcome of the immediate effect of acupuncture on relieving itch, and the resting-state scanning data after 0−/2−/4-week interventions will be the primary mechanistic outcome of acupuncture’s long-term effect on UP.

Patients will undergo three fNIRS recording sessions. Each fNIRS scan will be scheduled on non-dialysis days or before dialysis sessions to minimize the influence of acute biochemical fluctuations. The first fNIRS scan will be conducted before the long-term acupuncture treatment, including an 8 min rest scanning and a 5 min task scanning during acupuncture treatment with immediate itch induction by the cowhage test (Figure 2A). Another two fNIRS scans will be performed after the 6th and 12th long-term acupuncture treatments, with only the 8 min rest scanning.

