### Study design

2.1

This is a randomized clinical trial based on fNIRS, and a total of 96 patients with UP will be enrolled. Patients will be randomly divided into three groups (VA, SA, or WT groups) in a ratio of 1:1:1 after meeting the inclusion criteria. Participants in the VA and SA groups will receive one session of immediate verum or sham acupuncture during scanning, followed by 4 weeks of long-term verum or sham acupuncture treatment, respectively. The clinical evaluation and fNIRS scans are presented in Figure 1 and Table 1. The study is following the Standard Protocol Project Items: Recommendations for Intervention Trials (SPIRIT) guidelines, the principles of Consolidated Standards of Reporting Trials (CONSORT), and the Standards for Reporting Interventions in Clinical Trials of Acupuncture (STRICTA).

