### Blinding

2.7

Since the acupuncturist is always aware of the grouping of patients, the acupuncture manipulation will be concealed from participants, researchers, outcome evaluators, and statisticians. Researchers, the acupuncturist, outcome evaluators, and statisticians are separate. To minimize non-specific effects arising from acupuncturist-participant interaction, a standardized communication script will be implemented across all groups, restricting conversation to neutral, pre-specified phrases (e.g., greeting, procedural instructions, and safety checks only). To assess blinding success, after completion of the 4-week trial and final clinical assessment, participants in the VA and SA groups will be asked to guess whether they received verum acupuncture, sham acupuncture, or were unaware of it; the Bang blinding index will then be calculated for these two groups.

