### Limitations

3.4

However, several limitations should be acknowledged and managed. Firstly, uremic toxin level fluctuations in hemodialysis patients may affect cerebral hemodynamics. To address this, we will define strict dialysis adequacy criteria (spKt/V ≥ 1.2) in the inclusion criteria. Secondly, although the cowhage-induced itch model reliably activates non-histaminergic pruriceptive pathways relevant to UP, its intensity and temporal profile may differ from spontaneous uremic itch. Therefore, to address this limitation, we will perform additional analyses of resting-state brain activity and spontaneous itch perception during needle retention. In addition, with a detection depth of 20 mm approximately, fNIRS primarily measures cortical hemodynamics and cannot directly assess subcortical itch-related regions, such as the thalamus, insula, and brainstem. Future studies may utilize neuroimaging techniques with higher spatial resolution (e.g., fMRI) or multimodal approaches (e.g., fMRI-EEG) to further explore the central mechanisms of acupuncture for UP.

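### Nothing holds a patient's three fNIRS scans to the same point of the dialysis cycle, which can add avoidable within-patient noise to the resting-state outcome

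*Protocol article*

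**What the plan says.** Section 2.11 states: "Patients will undergo three fNIRS recording sessions". The resting-state data from weeks 0, 2 and 4 "will be the primary mechanistic outcome of acupuncture’s long-term effect on UP". On timing it says: "Each fNIRS scan will be scheduled on non-dialysis days or before dialysis sessions to minimize the influence of acute biochemical fluctuations". On the later scans: "Another two fNIRS scans will be performed after the 6th and 12th long-term acupuncture treatments".

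The waiting-list arm has no such sessions. Section 2.9.2.3 says: "Patients assigned to the WT group will not receive any acupuncture treatment at the cowhage test or during the 4-week trial". Its scans are placed only by week, in Table 1.

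Section 3.4 concedes that "uremic toxin level fluctuations in hemodialysis patients may affect cerebral hemodynamics". The remedy it names is dialysis adequacy at entry (spKt/V of at least 1.2). Under section 2.4.2 this has to be met at least once in the 3 months before enrolment.

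Section 2.14.2 analyses the resting-state measures with a linear mixed model containing time, group, their interaction and a random intercept per participant. There is no term for dialysis state or time since dialysis.

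**The concern.** The aim of the timing rule is sound, and the rule does useful work: it rules out scans during dialysis, or after it on the same day. But a patient scanned on a non-dialysis day at week 0 and before a dialysis session at week 4 complies fully. Those two scans can lie at different distances from the last dialysis, and that is the kind of fluctuation the rule is meant to limit.

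The outcome is analysed as change within patients. A random intercept absorbs stable differences between patients but not a change of state between one patient's scans. An entry criterion met once before enrolment cannot control that state either. At stake is precision on the primary mechanistic outcome, in a trial whose stated aim is mechanism.

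**Working it through.** **1. Is there a plan figure to reproduce?** None for fNIRS. The only stated sample size (section 2.5) is for 24 h-WI-NRS. It reproduces: pooled SD = √((1.30² + 2.55²)/2) = 2.02; d = (3.68 − 1.64)/2.02 = 1.01; a two-sided t-test at 0.05 with power 0.95 needs 27 per group (power 0.954); 27/0.85 = 31.8, so 32 per group and 96 in total. Scan timing plays no part in it.

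**2. Which fNIRS measures are exposed?** Section 2.14.2 defines two resting-state measures.
- *Regional HbO* is the temporal mean over the rest period. The optical density signal is band-pass filtered at 0.01–0.2 Hz before conversion to HbO. A constant offset between scan days lies at zero frequency, so the filter largely removes it.
- *Functional connectivity* is the Fisher-transformed correlation between channel time series. It depends on fluctuations inside the pass band, so the filter does not protect it from a change of state.

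The immediate outcome is task minus rest within the first session, so no change of state between scans enters it.

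**3. Noise, as an illustration.** Assumptions, none of them from the documents: the measure shifts by s within-patient SDs (σ) between the two permitted slots; each scan is equally likely to be in either; r is the correlation of slots between two scans of one patient.

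Variance of a two-scan change = 2σ² + s²σ² × 2 × 0.25 × (1 − r), so its ratio to 2σ² is 1 + 0.25s²(1 − r).

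| s | r = 0 | r = 0.5 | r = 1 |
|---|---|---|---|
| 0.5 | 1.06 | 1.03 | 1.00 |
| 1.0 | 1.25 | 1.13 | 1.00 |
| 1.5 | 1.56 | 1.28 | 1.00 |

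The equivalent loss of sample size is 1 − 1/ratio. At r = 0 this is 6%, 20% and 36%; at r = 0.5 it is 3%, 11% and 22%.

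**4. Bias: when would it arise?** Let p be the share of an arm's scans in one slot. The bias in a group-by-time contrast between arms A and B is

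s × [(p_A,later − p_A,week 0) − (p_B,later − p_B,week 0)].

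- A 30-point gap present at both scans gives s × (0.30 − 0.30) = 0.
- A 30-point gap at the later scan with none at week 0 gives 0.30s: 0.15σ at s = 0.5 and 0.30σ at s = 1. Dividing by √2 puts these on the change-score SD, before added noise: 0.11 and 0.21.

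So an arm difference in slot mix matters only if it changes between scans.

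**5. Does the text offer a route to such a change?**
- *VA versus SA:* both arms have 12 sessions at three per week, and both have later scans anchored to sessions 6 and 12. No systematic route is shown.
- *VA or SA versus WT:* the week-0 scan precedes the treatment course in every arm, but the later scans are tied to sessions in VA and SA and to nothing but the week in WT. The slot mix could therefore move over time in one and not the other. This is possible, not demonstrated.

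**The case against.** **A condensed article may leave finer scheduling to the full protocol.** This is fair for a case report field or a booking procedure. But the article itself states the rule, its purpose and the model terms, and the rule as stated does not fully serve its purpose. That part stands as a finding.

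**A reader might infer that the arms will differ because scans follow randomisation.** They do follow it: section 2.1 says "Participants in the VA and SA groups will receive one session of immediate verum or sham acupuncture during scanning", so even the first scan comes after allocation. That alone creates no imbalance. The article does not say when or by whom scan days are chosen, VA and SA share their anchors, and section 2.7 states that "the acupuncture manipulation will be concealed from participants, researchers, outcome evaluators, and statisticians". A VA versus SA bias is not supported. Blinding to the manipulation does not close the WT route, which would come from visit logistics, but section 2.5 gives WT only an auxiliary role in the clinical comparison.

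**The level-shift model fits regional HbO poorly.** Correct, because of the filter. The variance figures should be read as applying to connectivity, and only if state alters it.

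**The figures are hypothetical.** Also correct. A patient on a regular dialysis timetable may be booked alike each time, which raises r and shrinks the effect, to zero at r = 1.

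**Slot matching could conflict with the session anchors.** The text says only that these scans come after sessions 6 and 12, not how soon, so there is some room to do both.

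**Conclusion.** The point holds as one of avoidable noise. Two dialysis-cycle slots are allowed, nothing ties a patient's scans to one, the model has no term for it, and the article itself says such fluctuation may affect the signal. The exposed measure is chiefly functional connectivity at weeks 0, 2 and 4.

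The size is unknown. The illustrated range runs from no inflation of the change variance to 56%, depending wholly on an assumed shift and on how consistently patients happen to be booked. Bias in group-by-time needs an arm difference in slot mix that changes between scans; the only possible route in the text is VA or SA against WT. The 24 h-WI-NRS analysis, the sample size and the task-minus-rest outcome are untouched. This is a moderate improvement to a mechanistic outcome, best made before scanning starts.

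**What to change.** 1. Schedule each patient's week-2 and week-4 scans in the same dialysis-cycle slot as that patient's week-0 scan, in all three arms including WT, within the existing session-6 and session-12 anchors for VA and SA.
2. Record hours since last dialysis at every scan. This is easier to capture then than to reconstruct later.
3. Add that variable as a time-varying covariate in the resting-state mixed model, at least as a sensitivity analysis. With slots matched it will mainly pick up departures from the schedule.

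The cost is less freedom in booking scans, one case report field and one model term. No treatment or dialysis schedule changes.
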